**8. PET Data Acquisition**

Acquire clinically acceptable scans in 2D or 3D mode.

**9. Post-Scan Procedure**

**a) Vitals**

Heart rate, blood pressure and temperature will be taken post-scan.

**b) Adverse Event Reporting**

If the patient experiences any adverse events related to the scanning procedure, record the events on the *Adverse Event* Case Report Form.

**c) Rehydration**

Patients should be offered juice or water if necessary.

## APPENDIX VII: FDG PET IMAGE INTERPRETATION

To ensure quality control of PET interpretation, a sample of PET scans will be independently interpreted by a primary nuclear medicine physician at the enrolling Clinical Centre and a secondary nuclear medicine physician from an external centre with compatible PET equipment.

Only the primary reading will affect patient management. The secondary reading will be performed on digital images transferred by compact disc. The secondary readers will be provided with the data required for scanning (e.g. height and weight) and scanning details (e.g. injected FDG dose), as well as a short description of relevant clinical findings important for interpretation of the PET results, prepared by the local PET Reader (e.g., information about recent surgery that may be similar in appearance to a tumour on the PET image).

Whole body PET-CT scans will be interpreted based on attenuation-corrected and non-attenuation-corrected results. The reader's degree of suspicion for an abnormality will be recorded as per image interpretation guidelines specified in section 7.3 with use of a **5-point ordinal categoric scale**, with the following categories: 0-normal, 1-probably normal, 2-equivocal, 3-probably abnormal and 4-definitely abnormal.

**For all lesions**, semi-quantitative measurement of the **single-pixel maximal standard uptake value normalized to body mass** will be performed on the primary tumour. The SUVBM is calculated using the tumour radioconcentration Q (Bq/cc), body mass m (kg) and injected activity Qinj (Bq):

$$\text{SUV}_{\text{BM}} = (Q / Q_{\text{inj}}) \times m \times 1000$$

The transaxial slice number that contains the single pixel maximal SUV will also be identified. **SUV should be measured with an ROI to encompass at most 2/3 of the diameter of the node to minimize partial volume effects.**

**As there may be variability in SUV measurements between different PET centres and between different studies, 2 measurements of SUV of the liver should also be recorded as normal reference. A 3 cm diameter region of interest in the right lobe of the liver should be used for these 2 measurements.**

Recorded data will be transmitted to OCOG either on paper case report forms or through EDC. OCOG will evaluate both interpretations and determine if there are any major discrepancies. Examples of major discrepancies are (a) a difference in the location of abnormality and (b) a difference of more than 1 point in the 5-point ordinal categorical scale (e.g. 2-equivocal vs. 4-definitely abnormal).

Major discrepancies between the primary and secondary readers will be resolved by consensus between the two readers. Meetings to discuss scans will be coordinated by OCOG

## APPENDIX VIII: AMINOGLYCOSIDE ANTIBIOTICS

| Generic | Brand Name             |
|-----------------------|--------------------------------------|
| Amikacin       | Amikin                        |
| Gentamicin     | Garamycin, G-Mycin, Jenamicin |
| Kanamycin      | Kantrex                       |
| Neomycin       | Mycifradin, Myciguent         |
| Netilmicin     | Netromycin                    |
| Paramomycin    |                                      |
| Streptomycin   |                                      |
| Tobramycin     | Nebcin                        |

## APPENDIX IX: ECONOMIC ANALYSIS

### Economic Evaluation

#### Costs

We have recently worked with Decision Support Services at Hamilton Health Sciences to successfully obtain costs for treatments, tests, medications, hospitalizations from the Ontario Case Costing Data Base for two of OCOG's other PET trials in lung cancer and breast cancer. We will use the same approach for this trial for costs related to hospitalizations, tests, procedures, medications and the use of other healthcare services. Costs related to physician services will be taken from the recent OHIP payment schedule. For chemotherapy costs we will employ a bottom up costing approach. For radiotherapy costs, we will review funding relationships between individual cancer centres, CCO and the MOHLTC to determine appropriate costs. For example, currently the MOHLTC reimburses cancer centres \$3500 per new patient radiated.

Total healthcare cost including all imaging and treatment will be calculated for each patient and averaged across patients in each study arm. Once patients develop recurrence of their cancer, treatments will vary. We will capture what treatments were received and obtain costs estimates for these but further data collection will not take place.

In addition to the two cancer specific QoL questionnaires, utilities will be estimated using the EQ-5D measurement system. The EQ-5D is a reliable and valid questionnaire designed to estimate societal valuations of the quality of life of patients (utilities). For this analysis, the UK tariff for estimation of utilities will be adopted. The EQ5D will be used to estimate utility values at each assessment point. These will then be aggregated using area under the curve methodology controlling for baseline utility value to allow estimation of quality adjusted life years (QALYs).

#### Analysis

Analysis will take the form of a traditional concurrent clinical and economic evaluation with prospective follow-up of patients. The economic evaluation will follow Canadian guidance on the conduct of such studies. Analysis will take the form of both a cost effectiveness and a cost utility analysis.

For the cost effectiveness analysis, effectiveness will be assessed by the primary outcome of the clinical trial; the treatment delivered based on an imaging strategy. The analysis will assess the incremental costs associated in delivering either chemo-radiotherapy with extended field radiation or avoiding radical chemo-radiotherapy of curative intent and proceeding to palliation or non-curative chemotherapy or radiation versus standard curative chemo-radiotherapy. This will be estimated by:

$$\frac{C_{\text{PET-CT}} - C_{\text{CT}}}{E_{\text{PET-CT}} - E_{\text{CT}}}$$

Where:

$\underline{C_{\text{PET-CT}}}$  = average total costs for patients randomized to the CT abdomen and pelvis plus PET-CT arm – including all imaging and subsequent treatment

$\underline{C_{\text{CT}}}$  = average total costs for patients randomized to the CT abdomen and pelvis arm

$\underline{E_{\text{PET-CT}}}$  = Probability of change in management based on an imaging strategy for patients randomized to the CT abdomen and pelvis plus PET-CT arm

$\underline{E_{\text{CT}}}$  = Probability of change in management based on an imaging strategy for patients randomized to the CT abdomen and pelvis arm

For the cost utility analysis effectiveness will be assessed by QALYs as described in the Quality of Life analysis section. This will be estimated by:

$$\frac{\underline{C_{\text{PET-CT}}} - \underline{C_{\text{CT}}}}{\underline{\text{QALY}_{\text{PET-CT}}} - \underline{\text{QALY}_{\text{CT}}}}$$

Where:

$\text{QALY}_{\text{PET-CT}}$  = Average total QALYs for patients randomized to the CT abdomen and pelvis plus PET-CT arm

$\text{QALY}_{\text{CT}}$  = Average total QALYs for patients randomized to the CT abdomen and pelvis arm

### Time Horizon

Primary analysis will have a time horizon of two years reflective of the period of data capture within the clinical trial. Secondary analysis will involve forecasting costs and utility values up to a time horizon of ten years. Costs and benefits will be discounted at 5%.

### Perspective

Analysis will be conducted from the healthcare system perspective.

### Analysis of Uncertainty

The uncertainty concerning the incremental cost, the incremental effectiveness and the incremental cost-effectiveness ratio will be estimated by conducting probabilistic analysis through non-parametric bootstrapping. Bootstrapping allows estimation of the dispersion around an outcome of interest. With bootstrapping, the study sample is treated as the patient population. We then re-estimate the study sample through drawing repeated random samples of the same size as the original sample. This is done by drawing individual patient samples with replacement from the original data.

For this study, we will obtain 5,000 estimates of costs and effectiveness (each of the primary and secondary outcomes) for each strategy. This approach will be used to derive 95% certainty intervals around the difference in costs, outcomes and, where pertinent, the incremental cost per outcome. These certainty intervals will be estimated using the bias corrected percentile method.

Results from the bootstrapping exercise will also be used to depict cost effectiveness acceptability curves (CEACs). CEACs are a graphical representation of the probability that a treatment may be cost effective given alternate dollar values placed on an outcome. This will allow estimation of the probability that the experimental treatment can be considered cost effective given the available data.

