All tests will be two-sided and based on an intent-to-treat analysis. A p-value of 0.05 or less will be considered statistically significant. In addition, 95% confidence intervals will be constructed for outcomes of interest. All data analysis will be performed using the latest versions of SAS (Cary, NC) and using StatXact (Boston, MA).

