### **13.2. Sample Size and Feasibility**

It is postulated that approximately 25% of patients having the CT of the abdomen and pelvis alone will receive either palliative care (~10%) or EFRT (~15%). The use PET-CT in addition to CT of the abdomen and pelvis would be considered valuable if the proportion of patients treated with either palliative care or EFRT increased to 45% (20% and 25% respectively). These estimates are derived using the estimates available from the previous smaller studies performed on the older PET scanners. Further, a 20% absolute difference was felt to be a clinically important difference and is slightly more conservative than the 50% relative change in treatment rate observed in the OCOG trial of PET in early lung cancer. Based on these considerations, a trial with 288 patients (192 PET-CT, 96 CT abdomen and pelvis) will have over 90% power to detect a difference of this magnitude using the Fisher's exact test ( $\alpha=0.05$ , two-sided).

The 2:1 randomization for this trial allows us to gain additional understanding of the potential effect of FDG PET-CT plus CT of the abdomen and pelvis to CT of the abdomen and pelvis alone, which is currently the standard of care in patients with locally advanced cancer of the cervix. Using this unbalanced allocation will increase the number of patients who receive FDG PET-CT and could potentially help with recruitment. We feel this is ethical as preliminary data indicate the use of PET-CT may be better than CT abdomen and pelvis alone and it is unlikely that PET-CT will be detrimental to the individual patient. (Although unlikely to be detrimental, it is unclear that there is a benefit and even if a benefit exists, whether it is sufficient to warrant extensive use of PET-CT, hence the rationale for the study).

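### The bias-corrected percentile interval planned for cost per QALY falls well short of 95% coverage if the true QALY difference is small

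*Protocol*

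**What the plan says.** Appendix IX (Analysis) defines two ratios. Both have the difference in mean total cost between the arms as numerator. The cost-effectiveness ratio divides it by the difference in the probability of a change in management, the cost-utility ratio by the difference in mean QALYs.

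Under Analysis of Uncertainty, patients are resampled to give 5,000 replicates, and: "This approach will be used to derive 95% certainty intervals around the difference in costs, outcomes and, where pertinent, the incremental cost per outcome". The method is then fixed: "These certainty intervals will be estimated using the bias corrected percentile method". The same replicates feed cost-effectiveness acceptability curves. The protocol has no rule for replicates with a negative or near-zero QALY difference, and it does not say when a ratio interval counts as pertinent.

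On the horizon: "Primary analysis will have a time horizon of two years reflective of the period of data capture within the clinical trial". A ten-year projection is secondary. Section 13.2 sizes the trial on treatment delivered only: "a trial with 288 patients (192 PET-CT, 96 CT abdomen and pelvis) will have over 90% power".

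**The concern.** A percentile interval for a ratio is read off the ordered replicate ratios. That order means something only while the denominator keeps one sign. Once some replicates have a negative QALY difference, a result that costs more and loses health has a negative ratio and lands at the low, apparently favourable, end of the ranking, where a cost-saving and health-gaining result would also sit.

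The bias correction uses the share of replicates ranked below the point estimate. It treats a departure of that share from one half as bias in the estimate. Here the departure comes largely from misplaced replicates, so the correction moves both limits for no good reason.

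Section 15 says the results will inform policy makers on adding PET-CT. A cost-per-QALY interval labelled 95% that often excludes the true value would misstate how uncertain that figure is.

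**Working it through.** **1. The plan's own figure.** For 25% versus 45% (Section 13.2), two-sided 5%, exact Fisher power is 91.5% at 192/96 and 90.3% at 128/128. The stated sample size reproduces. It says nothing about QALYs.

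**2. Distance of each denominator from zero.** At 192/96, SE = SD × √(1/192 + 1/96) = SD × 0.125.
- Change in management: SE = √(0.25×0.75/96 + 0.45×0.55/192) = 0.057, so the planned 0.20 lies 0.20/0.057 = 3.5 SE from zero.
- QALYs: an assumed two-year SD of 0.3, 0.4, 0.5 or 0.6 gives an SE of 0.0375, 0.050, 0.0625 or 0.075.

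**3. Plausible size of the QALY difference.** Section 13.2 expects EFRT to rise from 15% to 25% and palliative care from 10% to 20%. One full extra QALY within two years for each additional EFRT patient gives 0.10 × 1 = 0.10 on average: 1.6 SE at SD 0.5 and 2.7 SE at SD 0.3. Reaching 2 SE at SD 0.5 (0.125) needs 0.125/0.20 = 0.625 QALY per patient whose management changes. Section 13.2 itself calls it unclear whether there is a benefit.

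**4. How the correction fails.** The constant is z₀ = Φ⁻¹(share of replicate ratios below the estimate), and the limits are the replicate percentiles Φ(2z₀ ± 1.96). For illustration, treat the cost difference as positive and known, measure the QALY difference in SE units, and let the truth be 0.8 SE (0.05 at SD 0.5).
- *Estimate −0.3 SE.* The share below it is Φ(0.3) − 0.5 = 0.118, so z₀ = −1.185. The upper limit is at percentile Φ(−2.37 + 1.96) = 0.34. But Φ(0.3) = 62% of the ratios are negative, so the whole interval is negative and excludes the true positive ratio. The plain 97.5th percentile would be positive and the plain interval would include the truth.
- *Estimate +0.1 SE.* The share below it is Φ(−0.1) + 0.5 = 0.960, so z₀ = 1.75. The lower limit is at percentile Φ(3.51 − 1.96) = 0.94. The true ratio sits at percentile Φ(−0.1) + 1 − Φ(0.7) = 0.70 and is excluded.
- *All estimates.* The interval misses when the estimate is below −1.62, between −1.04 and 0.28, or above 2.72 SE. Around a truth of 0.8, this has probability 0.008 + 0.267 + 0.027 = 0.30.

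**5. Simulation, patients resampled within arm, 192/96.** Assumed: lognormal costs with mean 20,000 and CV 0.5, cost difference 2,000, cost–QALY correlation −0.2. Miss rate of the nominal 95% bias-corrected interval:

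| True QALY difference | All trials, SD 0.3 | All trials, SD 0.5 | Both estimates positive, SD 0.3 | Both estimates positive, SD 0.5 |
|---|---|---|---|---|
| 0.02 | 39.1% | 47.5% | 15.0% | 14.8% |
| 0.05 | 16.1% | 29.5% | 8.2% | 12.5% |
| 0.10 | 5.4% | 12.9% | 2.7% | 8.0% |
| 0.20 | 5.5% | 4.6% | 3.5% | 2.4% |

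On the same trials the bootstrap interval for net monetary benefit, taken at the true ratio, missed in 3.7–6.2%.

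**6. Cross-checks.**
- A second patient-level simulation used beta QALYs, gamma costs, a cost SD of 15,000 and 5,000 replicates. It gave 34.7% at 0.03 QALY (SD 0.5), 21.5–28.3% at 0.05 (SD 0.4–0.6), 6.2–11.4% at 0.10 (SD 0.4–0.5) and 5.1% at 0.20 (SD 0.5). With a cost difference of 4 SE and 0.05 QALY (SD 0.5) it gave 31.0%, in line with the 30% in step 4. The plain percentile interval missed in 1.4–4.5%, Fieller's in 4.3–6.5%.
- Normal-theory runs (cost SD 10,000) gave 38–49% at 0.02, 17–30% at 0.05, 5–14% at 0.10 and 3–5% at 0.20. The plain percentile interval missed in 2–9% and Fieller's in 4–6%.

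**The case against.** - **The size rests on assumed inputs.** This stands. The documents give no QALY or cost figures, and the problem fades at 2–3 SE. Appendix IX controls for baseline utility when estimating QALYs, which would reduce the SE. The QoL Analysis set can only be the same size as the randomized set or smaller, which works the other way. The ten-year projection was not examined.
- **The ratio interval is promised only where pertinent.** Read generously, this means only when both estimated differences are positive. The miss rate then still stays at about 9–16% for true differences of 0.02–0.05. Fieller's interval misses 2–3% under the same restriction, so the excess belongs to the method and not to the selection.
- **Valid displays are already planned.** The separate intervals for cost and outcome differences stand. At each threshold the acceptability curve is the bootstrap probability that net benefit is positive, so it has no ordering problem. This limits the harm, but it does not replace the stated interval.
- **A reader might infer that ranking by the raw ratio is enough to destroy coverage.** The calculations do not support that. A plain percentile interval on the same ranking misses only about 2–9%. The undercoverage comes from the bias correction acting on a ratio that is not ordered. Dominant replicates need not be present: they were 0.2% of replicates in the 31.0% setting. What remains wrong with the plain interval is that a negative limit can mean either dominance or being dominated.
- **A reader might also take the one earlier randomized trial as evidence that the QALY difference is nil.** It found no survival difference, but Section 1.5 calls it under-powered and limited to women with positive pelvic nodes.

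**Conclusion.** The point holds for the cost-per-QALY interval. The method that Appendix IX fixes for it undercovers when the true two-year QALY difference is below about 2 SE. That is a plausible case given the shift in treatment the plan itself expects. Under the assumptions stated, the miss rate is about 38–49% at 0.02 QALY, 17–30% at 0.05 and 5–14% at 0.10, and near nominal by about 3 SE.

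The documents do not support extending this to the whole economic analysis. Cost per change in management, with a planned difference 3.5 SE from zero, is essentially unaffected. The difference intervals and the acceptability curve stand. The primary outcome, EFS, OS and QoL analyses are not involved. It is a minor-to-moderate correction within secondary objective 4.

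**What to change.** In Appendix IX, Analysis of Uncertainty:
- Keep the 5,000 replicates and the intervals for the cost and outcome differences.
- Delete the bias-corrected percentile interval for cost per QALY.
- Report in its place, in every case, the bootstrap interval for incremental net monetary benefit (threshold × QALY difference − cost difference) at stated willingness-to-pay values, or the Fieller set for the ratio, or both. State when the Fieller set is unbounded.
- Show the replicates on the cost-effectiveness plane next to the planned acceptability curve.

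Do not make the ratio interval conditional on a high share of replicates with a positive QALY difference. Mostly trials that overestimate the benefit pass such a gate. Among trials with at least 97.5% positive replicates, even Fieller's interval misses in 33–53% at 0.02 QALY and 8–20% at 0.05.

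The cost is a change of wording, with no new data. The small downside is that a single bounded interval for cost per QALY may not be reportable.
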